### Procedures

After interested participants contact the research assistant and are determined to be eligible to participate in the study, (and provide an approximate date for contact 2 months post-baby) we schedule a fitness test at our lab. At the initial visit to the lab, signed informed consent is obtained from participants by the project coordinator after overviewing the requirements of the study. Participants are assigned an identification number and all data is attached to this number to ensure confidentiality. A qualified exercise professional is employed to ensure consistency of the fitness testing procedures [68] and is also present at the first initial meeting. This individual is responsible for quality control throughout the fitness-testing portion of the trial. The fitness testers are blind to the treatment conditions of the participants. Both parents are given accelerometers to wear for 1 week and instructed on how to enter information about each day’s activity in a log. Fitness testers provide a short training session on how to wear and use the accelerometers. After the 1 week wear of accelerometers, participants are randomized at a 1:1 ratio to either intervention or control group, using an online randomizer program. Participants as well as the research assistants and project coordinator are aware of the group allocations, but all fitness testers are blinded to treatment allocation. The project coordinator and research assistants have to be aware of the condition to which participants are randomized in order to deliver the appropriate materials. The project coordinator and research assistant meet with participants at their home or location of choice to go through their specific intervention materials. Two people attend the house visits for safety reasons.

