### Analysis strategy

Missing data will be evaluated for patterns of missingness for each psychosocial variable and behavior at all time points using the dummy coding procedures of Allison [2]. Depending on the outcome of these tests (e.g., missing at random, missing completely at random, etc.) we will initiate the appropriate missing data handling strategy. Intention to treat analyses will also be performed in addition to sensitivity analysis procedures. An assessment of covariates will also be performed. As one would expect during early parenthood many factors may contribute to inactivity which include but are not limited to child care status, leave status, baseline quality of life and other general demographics. The RCT approach aids in some equalization in the group x time effect of these factors, yet it is acknowledged that some of these confounds may affect the time effect regardless of randomisation.

To address the first objective, hierarchical linear modeling will be used in HLM 6.0. First, a Level-1 no intercept model will be specified such that a main effect will be entered for father (0 = Mother; 1 = Father), Mother (0 = Father; 1 = Mother), a Father linear trend (0 = baseline; 1 = 6 months), and a Mother linear trend with all coefficients set to random. In this model, the main effects for the fathers and mothers’ intercepts represent their respective baseline minutes of MVPA, whereas the linear trends represent the change in MVPA (or not) over the 6-month interval. At Level-2, cross-level interactions will be added such that condition (0 = control; 1 = intervention) predicts the fathers’ Level-1 intercept / slope and the mothers’ Level-1 intercept / slope. These potential interactions will determine whether baseline MVPA is similar between conditions and whether the potential change in MVPA across time is similar between conditions accounting for the couple variation. Second, the fathers vs. mothers’ coefficients will be statistically compared using the multivariate hypothesis testing procedure (e.g., to determine if the magnitude of change in the minutes of MVPA is the same for fathers and mothers). Third, the correlations among the fathers and mothers’ intercepts and slopes will be examined to determine, for example, whether the mothers’ baseline minutes of MVPA are significantly associated with their own change in MVPA and / or their fathers’ change in MVPA (and vice versa).

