### Justification of sample size

It is recognized that two analytical approaches can be utilized in longitudinal couple studies within hierarchical linear modeling. First, a 3-level model can be created where repeated assessments (Level-1) are nested within the individual (Level-2) that are nested within the couple (Level-3) [4]. However, we have chosen to utilize the more common approach, which is to nest the individual repeated assessments (Level-1) within the couple (Level-2) ([4]; S. [43]). Therefore, we used the OpDes Program for power estimation of hierarchical linear models (S. W. [44]) to calculate the sample size needed for our analyses. Specifically, with a frequency of 4 measurement occasions, a duration of 6 months, within-person variance of 1.0, a growth rate of 1.0, and a moderate effect size (.40), a total of 200 couples (i.e., 100 couples per condition) are needed to show a significant adherence to MVPA as measured via accelerometry. The effect size represents the low-end of findings from prior intervention research with this demographic [17, 21, 22, 34, 38], yet it is clearly in the clinically meaningful range (D.E.R. [65]). These studies showed mean increases of moderate to vigorous physical activity of 80 min per week, which is over half of the recommended weekly activity for public health [62]. Our sample size includes a potential 25% attrition rate similar to the longitudinal study (thus total recruitment *N* = 267. The attrition in the prior trial was actually 15% [48], but we sought to oversample to accommodate the active component of this experimental trial compared to the prior passive prospective design. Our over-sampling procedures account for attrition due to second pregnancy or other possible reasons for drop out such as break-up, moving away, etc. The prediction-based research will be examined by group condition as well as via the collapsed sample for mediation analyses. Considering an average of five predictor IVs (TPB model), and using a small-medium effect size (f^2^ = .10) we will have sufficient power (.80) to evaluate these predictors at an alpha of .05. Our longitudinal study also supported the use of a small-medium effect size as an appropriate criterion [47]. Finally, the evaluation of physiological outcomes of participants across time will follow a 2 (condition) × 2 (time) interaction. The proposed sample size is, therefore, more than adequate to ensure sufficient statistical power for the physiological measurements.

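### Condition is allowed to predict baseline MVPA although couples are randomised after the baseline week: a baseline test without inferential use and an avoidable loss of precision of unstated size

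*Protocol article*

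**What the plan says.** The Procedures section of the protocol article fixes the order of events: "After the 1 week wear of accelerometers, participants are randomized at a 1:1 ratio to either intervention or control group". Allocation therefore comes after baseline MVPA has been recorded.

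The Analysis strategy section sets up a no-intercept model with separate father and mother terms. Time starts at zero at the baseline visit ("a Father linear trend (0 = baseline; 1 = 6 months"), so each parent's intercept is that parent's baseline MVPA. At Level 2, "cross-level interactions will be added such that condition (0 = control; 1 = intervention) predicts" the intercept and the slope of each parent. The intercept terms are given an explicit purpose: "These potential interactions will determine whether baseline MVPA is similar between conditions". The treatment effect is the condition effect on the linear trend.

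The section states no common baseline mean across arms. It announces an assessment of covariates, but baseline MVPA is not among the covariates it names. The same approach is carried over to the motivational, quality-of-life and fitness outcomes.

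**The concern.** With allocation after the baseline week, the two arms have the same expected baseline MVPA. Any observed difference is chance. The plan nevertheless estimates a condition effect on baseline for fathers and for mothers and uses it to judge similarity. That tests, twice, a null hypothesis already known to be true.

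Two things are at stake. First, estimated intercepts and slopes are generally correlated. A model that knows the baseline means are equal can use a chance baseline difference to sharpen the slope contrast, and a model with free baseline means cannot. Second, the intercept here is a fitted value on a straight line and not the observed baseline mean. The Hypotheses section allows that the effect may wane. An effect that appears early and then shrinks is not linear from zero, so part of it can be pushed into the condition-by-intercept term and be read as failed randomisation.

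**Working it through.** **1. The plan's own figure.** Inputs from Justification of sample size: "with a frequency of 4 measurement occasions, a duration of 6 months, within-person variance of 1.0, a growth rate of 1.0", "a moderate effect size (.40"), and "a total of 200 couples (i.e., 100 couples per condition) are needed". Power and alpha are given only for the prediction analyses ("we will have sufficient power (.80) to evaluate these predictors at an alpha of .05"). I assume two-sided .05 and power .80 for the primary analysis too.

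- Simple two-mean formula: 2 × (1.96 + 0.84)² / .40² ≈ 98.1, so 99 per arm, or 198 couples. Power with 100 per arm is .807.
- Growth formula, reading the growth rate of 1.0 as slope variance τ = 1 and time in months: noncentrality = nδ²τ / [4(τ + V)], with V = 1/Σ(t − t̄)². For visits at 0, 1.5, 3 and 6 months, t̄ = 2.625, Σ(t − t̄)² = 19.6875 and V = .0508. Noncentrality = 200 × .16 / (4 × 1.0508) = 7.61, and power is .784. If a frequency of 4 means four per month over 6 months (25 occasions), power is .799.
- Attrition: 200 / .75 = 267.

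The stated 200 and 267 therefore reproduce, and they do so from the contrast with free baseline means. On a 0-to-1 time scale the same inputs would give power of only .387, so months is the reading used below.

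**2. What a common baseline mean changes.** Let A be the covariance matrix of a unit's estimated intercept and slope. The slope-difference variance is proportional to A22 with free baseline means and to A22(1 − ρ²) with a common mean, where ρ = A12/√(A11·A22). The ratio 1 − ρ² never exceeds 1.

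**3. On the stated growth inputs** (ASSUMED intercept variance 1; τ01 is the true intercept-slope correlation). A11 = 1 + .60 = 1.60, A12 = τ01 − .1333, A22 = 1.0508.

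| τ01 (assumed) | ρ | 1 − ρ² | Power at 200 couples |
|---|---|---|---|
| free baseline means | – | – | .784 |
| 0 | −.103 | .989 | .788 |
| −.2 | −.257 | .934 | .811 |
| −.3 | −.334 | .888 | .830 |
| −.4 | −.411 | .831 | .854 |
| −.5 | −.488 | .761 | .882 |

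The gain runs from 0.4 points to about 10 points. With intercept variance 4, power after the change is similar (.786 at 0, .893 at −.5). On the 0-to-1 time scale the gain at zero correlation would be larger (.387 to .439), but that reading does not reproduce the plan's figure.

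**4. Under ASSUMED equal correlation r between visits.** With time scaled 0 to 1, A11 = .6 + .4r, A12 = −.8(1 − r), A22 = 1.8286(1 − r). The ratio is 1 − .35(1 − r)/(.6 + .4r). For r = .5: 1 − .175/.8 = .781. Power, starting from .80, is Φ(2.80/√ratio − 1.96).

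| r | Variance ratio | Power from .80 to |
|---|---|---|
| .3 | .66 | .93 |
| .5 | .78 | .89 |
| .6 | .83 | .87 |
| .7 | .88 | .85 |
| .8 | .92 | .83 |

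**5. If the effect wanes.** Take an illustrative true effect of 0, .6, .5, .4 SD at the four visits. The fitted line has slope .8625/19.6875 = .0438 per month, or .26 over 6 months, and intercept .375 − 2.625 × .0438 = .26. The free-intercept model thus reports a baseline difference of .26 SD that does not exist, and a slope effect of .26 against a true 6-month effect of .40. With a common intercept the 6-month effect is .47 at r = .3, .39 at r = .5 and .31 at r = .8. The z value at 200 couples is higher throughout: 1.64 to 3.58, 1.94 to 3.29, and 3.07 to 3.75.

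**The case against.** The strongest defence is that condition on both intercept and slope is a conventional growth-model specification. The slope contrast is a valid randomised comparison, and the trial was sized for roughly that contrast. All of this stands.

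A reader might infer more than the article supports, in four ways.

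- That the baseline data are wasted. They are not: baseline is the first occasion of every trend and helps to estimate each slope. Only the knowledge that the arms share one baseline mean goes unused.
- That the contrast is a change score, with the variance ratio (1 + ρ)/2 of a two-point design (ρ here being the correlation between baseline and 6 months). The planned analysis is a four-visit linear trend. At correlations .5, .6 and .7 the two-point formula gives .75, .80 and .85, against .78, .83 and .88 for the trend, so it overstates the gain.
- That a single power gain can be quoted. No intercept variance, intercept-slope correlation or between-visit correlation is given as a planning input. The r = .62 under Pilot research is offered as evidence of symmetry between mothers and fathers and cannot safely be used as one.
- That 200 couples is too few because of this. The figure reproduces without the common baseline mean.

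It can also be objected that, with a non-linear effect, a common intercept changes the slope estimate and not only its variance. That is true, and the recovered effect then depends on the correlation (.31 to .47 in the illustration). It is a reason to word the fix with care. It does not favour the free intercept, which in the same illustration gives a smaller z and a false imbalance.

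**Conclusion.** The point holds as a low-severity improvement that costs nothing in data. The plan tests baseline equality where randomisation already guarantees it in expectation, and it forgoes precision that a common baseline mean would give.

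The size cannot be fixed from the article. The variance ratio is about .66 to .92 for assumed equal between-visit correlations of .3 to .8, with power rising from .80 to between .93 and .83. On the stated growth inputs the gain is under one point if intercept and slope are uncorrelated. These figures rest on two-sided .05, the growth rate read as slope variance per month, and intercept variance assumed 1. Type I error is intact, the 200-couple figure is not wrong, and no bias is shown where the effect is linear from zero. If the effect wanes, as the Hypotheses section allows, the free intercept can hide part of it and present it as baseline imbalance. The size of that in step 5 is illustrative only.

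**What to change.** Remove condition as a predictor of the father and mother intercepts, so that each parent type has one baseline mean common to both arms. Keep condition on the two slopes. To allow for a waning effect, replace the single trend by separate post-baseline visit terms and let condition act on those, still with a common baseline mean. Describe baseline MVPA by arm in a table, without a test, and delete the statement that the interactions will determine baseline similarity. Apply the same change to the secondary outcomes that use this model.

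The first form deletes two model terms, and the second needs a slightly larger model. Both use data already collected and leave the sample size unchanged. The choice should be recorded before outcome data are examined by arm.

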**Methods:**

This study is a 6-month longitudinal randomized controlled trial. Parents are measured at baseline (2 months postpartum) with two assessment points at 6 weeks (3.5 months postpartum) and 3 months (5 months postpartum) and a final follow-up assessment at 6 months (8 months postpartum). The content of the theory-based intervention was derived from the results of our prior longitudinal trial of new parents using an adapted theory of planned behavior framework to predict changes in physical activity.

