The second section guides participants through the process of finding time and planning for postpartum physical activity as well as identifying barriers and strategies to meet recommended guidelines via self-regulatory approaches [28, 52, 59] both personally and as a couple. Participants brainstorm a list of potential and past barriers (and then strategies to overcome these) when setting their physical activity goals. This section is intended to target the control barriers of regular physical activity that were identified in our prior research on parents and to improve self-regulatory strategies. The content addresses social support strategies as a couple, with friends/or extended family, problem solving around bad weather, and low-cost activities as well as coping with fatigue. The section concludes with a discussion of a re-set day (often Sunday) where the couple can reorganize their physical activity goals and plans for the following week and reflect on what “worked” and what “didn’t work” from the previous week. The emphasis is placed on how the couple can support each other to overcome barriers to physical activity either by sharing responsibilities or doing more activity together. For an outline of the study materials, please see the Additional file 1 and for an outline of the consent form please see Additional file 2. The two booster sessions (6 weeks and 3 months) serve to re-open the dialogue and assess how the couple is proceeding with in-person meetings between the couple and the research assistant. The benefits of physical activity, enjoyable activities to do, and goal setting and problem solving between the participants is re-explored and alternative plans and solutions are discussed if needed.

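### The cross-partner baseline-change correlations come from a model that names no same-visit residual correlation between partners, so any shared good or bad weeks would bias them, by an amount the documents do not fix

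*Protocol article*

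**What the plan says.** All references are to the protocol article.

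- **Model (Analysis strategy).** Level 1, to be fitted in HLM 6.0, has no common intercept. It has a father and a mother main effect, "a Father linear trend (0 = baseline; 1 = 6 months), and a Mother linear trend with all coefficients set to random". Time is zero at baseline, so "the main effects for the fathers and mothers’ intercepts represent their respective baseline minutes of MVPA". Condition enters at Level 2.
- **Nesting (Justification of sample size).** A three-level model was considered, but the choice was "to nest the individual repeated assessments (Level-1) within the couple (Level-2").
- **Test at issue (Analysis strategy, third step under the first objective).** The intercept and slope correlations are examined. The question given as an illustration is "whether the mothers’ baseline minutes of MVPA are significantly associated with their own change in MVPA and / or their fathers’ change in MVPA". The same is asked with the parents' roles exchanged.
- **Visits (abstract, Methods).** Baseline, "two assessment points at 6 weeks (3.5 months postpartum) and 3 months (5 months postpartum"), and 6 months.
- **Same weeks (Procedures).** Both parents receive monitors for one week at baseline, and monitors are dropped at the couple's house for the 6-week and 3-month wear.

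No couple-by-visit effect and no residual covariance between partners is named. Season appears only as a Level-1 covariate for the fourth objective.

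**The concern.** In the model as described, similarity between partners can enter only through the covariances of the four random coefficients. Two parents measured in the same week share the weather, the infant's health and household events. If that makes their deviations in a given week move together, the model has nowhere to put it except those covariances.

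The direction follows from how a line is fitted. An intercept at baseline and a slope estimated from the same visits have negatively correlated errors. When the partners' residuals are positively correlated, that error correlation crosses over: a mother's estimated baseline appears negatively related to the father's estimated change, and the two slopes appear to track each other more closely than they do. The trial could then report that an active parent has a partner who declines, or that partners change almost in lockstep, when part or all of this is shared weeks.

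**Working it through.** **1. The plan's own figure.** Inputs from Justification of sample size: effect size d = 0.40, within-person variance 1.0, growth rate 1.0 (read here as slope variance τ; time unit not stated), 200 couples. Power .80 and alpha .05 are stated there for the predictor analyses and assumed to apply here too. The noncentrality is λ = N·d²·τ / [4(τ + V)], where V is the error variance of a slope.

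| Reading | V | λ at N = 200 | Power |
|---|---|---|---|
| τ = 1.0 per month, visits at 0, 1.5, 3, 6 | 0.0508 | 32/(4 × 1.0508) = 7.61 | .78 |
| τ = 1.0 on the 0-1 scale | 1.83 | 32/(4 × 2.83) = 2.83 | .39 |
| τ = 0.5 on the 0-1 scale | 1.83 | 16/(4 × 2.33) = 1.72 | .26 |

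Only the per-month reading reproduces 200 couples at about 80% power. Dropout: 200/0.75 = 267, as stated.

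**2. Leakage.** For times 0, .25, .5, 1 the sums are n = 4, Σt = 1.75, Σt² = 1.3125, with determinant 4 × 1.3125 − 1.75² = 2.1875. So (X'X)⁻¹ = [[0.60, −0.80], [−0.80, 1.83]]. With complete balanced data the model's cross-partner covariance estimate is the sample covariance of the per-person least-squares coefficients. Its expectation is the true value plus ρσ²(X'X)⁻¹, where ρ is the partners' residual correlation at the same visit and σ² the residual variance. The bias is therefore −0.80ρσ² for intercept-slope and +1.83ρσ² for slope-slope. In months, the determinant is 4 × 47.25 − 10.5² = 78.75, and the two terms are −10.5/78.75 = −0.133 and 4/78.75 = 0.0508.

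**3. False rejection of no baseline/partner-change link.** Assumptions: σ² = 1, intercept variance 1, 200 couples, true cross covariance 0, two-sided 5% Wald test (the article names no test). With bias b, SE² = [(1 + 0.60)(τ + V) + b²]/199. Example at ρ = 0.3, τ = 1 on the 0-1 scale: b = −0.24, SE = √[(1.6 × 2.83 + 0.058)/199] = 0.152, |b|/SE = 1.58, rejection 35%.

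| ρ | τ = 1.0 (0-1 scale) | τ = 0.25 (0-1 scale) | τ = 1.0 per month |
|---|---|---|---|
| 0 | 5% | 5% | 5% |
| 0.1 | 8% | 10% | 5% |
| 0.3 | 35% | 45% | 7% |
| 0.5 | 74% | 86% | 11% |

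Simulation (4,000 replicates, τ = 1) agrees: 4%, 8%, 35% and 75% on the 0-1 scale, and 4%, 5%, 7% and 11% per month. With 88 couples, the number who had completed, the 0-1 scale gives 15% at ρ = 0.3.

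**4. Direct fits.** One mixed-model fit to 1,500 simulated couples with true cross terms of 0 gave −0.33 and −0.23 at ρ = 0.3 (expected −0.24), against −0.04 and 0.09 at ρ = 0. Maximum-likelihood fits restricted to admissible covariance matrices, with likelihood-ratio tests (200 replicates, 200 couples, τ = 0.5 and 1 on the 0-1 scale), rejected in 5% at ρ = 0 and 24% to 35% at ρ = 0.3. There, a true slope-slope correlation of .30 was estimated at .78 to .91, and one of .62 at .92 to .95.

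**5. What is not affected.** The condition-by-slope test kept a level of about 5% to 6%. A parent's own baseline-change covariance averaged −0.30 for a true −0.30 in the step 3 simulations. One limit: at ρ = 0.3, τ = 1 and partner correlation .62, the implied slope covariance is .62 + .55 = 1.17, above the slope variance of 1. A fit held to admissible values must then compromise elsewhere. The single direct fit gave own covariances of −0.46 and −0.41, against −0.29 and −0.39 at ρ = 0.

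**6. With the residual correlation modelled.** Rejection was 4.0% to 5.5% for every ρ from 0 to 0.5 at 88 and 200 couples. In the likelihood-ratio runs it was 6% to 8% (simulation standard error about 1.5 points).

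**The case against.** The strongest reply is that the article never says the partners' residuals are independent. It is a condensed account, and the residual structure could be set in a fuller analysis plan. That stands as a limit. But the article does go further than silence: it names the software, writes out the random part, explains the choice of nesting and states the comparison to be made. Run as described, that model has the bias whenever ρ is not zero.

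Several stronger readings are tempting and the documents do not support them:

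- **That the test will reject falsely.** No ρ is given. The r = .62 under Pilot research concerns slopes and intercepts, not weekly residuals. At ρ = 0 nothing is wrong.
- **That ρ must be positive.** The workbook encourages support "either by sharing responsibilities or doing more activity together". Sharing responsibilities, with one parent minding the infant while the other exercises, could make ρ negative. The biases then change sign, although the rejection rate depends only on the size of ρ. Season as a covariate could absorb part of a shared weather effect.
- **That rates of 35% to 45% are the plan's own.** They use slope variances on the 0-1 scale. The reading that reproduces 200 couples gives 5% to 11%. That reading is a planning input, not an estimate: it equals a variance of 1.0 × 6² = 36 on the 0-1 scale against a residual variance of 1. It therefore does not settle the true size either.
- **That the couple rationale depends on these correlations.** Pilot research rests it on earlier studies. The correlations match none of the listed objectives or hypotheses.
- **That the treatment effect is compromised.** It is not (step 5 of the working).

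**Conclusion.** The point holds in a conditional form. If partners' residuals in the same week are correlated, the described model biases the cross-partner intercept-slope covariance by −0.80 times, and the slope-slope covariance by +1.83 times, the residual covariance. These multipliers follow from the visit times alone.

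The consequence for the test depends on ρ and the variances, none of which the documents establish. It ranges from negligible to serious: 5% to 11% rejection over ρ = 0 to 0.5 under the per-month reading, and 35% to 45% at ρ = 0.3 under slope variances of 1.0 to 0.25 on the 0-1 scale. The harm is confined to a follow-on description. The condition-by-slope comparison, and essentially each parent's own baseline-change covariance, are not affected. Priority is optional to low: worth doing because it is cheap, not because a main conclusion depends on it.

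**What to change.** In Analysis strategy, for the third step, state that the mother's and father's Level-1 residuals at the same visit are allowed to correlate and have role-specific variances (a 2 × 2 block per visit, or an equivalent couple-by-visit effect). Take the cross-partner intercept-slope and slope-slope correlations from that model. It is identified: eight observations per couple give 8 × 9/2 = 36 variances and covariances, for 10 random-effect and 3 residual parameters. If HLM 6.0 cannot fit it, use another mixed-model program for this step.

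The cost is one sentence, possibly a second package, two extra covariance parameters and about 2 points of power if the residuals are in fact independent. No new data are needed, and the condition-by-slope analysis can stay as written.
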